## Abstract

**Background:**

Physiotherapists are commonly involved in the management of patients immediately following lumbar spinal surgery. There is however, very little research to guide physiotherapy intervention in the acute post-operative period, and the advice provided to patients regarding post-operative walking and physical activity has been shown to be highly variable.

The primary aim of this research is to establish whether the amount of walking patients perform in the week following lumbar spinal surgery predicts improvement in function at 6 months.

**Methods:**

This study will be a prospective cohort study design, with a projected sample size of 250 participants. Patients undergoing surgery for the management of a disc prolapse, degenerative disc disease, lumbar spinal stenosis and/or degenerative spondylolysthesis will be invited to participate in this study.

Outcome measurement will take place pre-operatively and at six months post-operatively. The primary outcome variable will be self-reported function, measured using the Modified Oswestry Disability Questionnaire and the physical component summary of the SF-36.

Each participant will be fitted with an activPAL3 accelerometer to be worn for the first seven post-operative days. This accelerometer will record time spent in active versus sedentary postures, step count and time spent walking. Multivariable logistic regression analysis will be used to investigate the relationship between the total time spent walking over the first seven post-operative days, and outcome at six months.

**Discussion:**

The results from this research will help to guide patient management during the inpatient phase, by identifying patients who are at risk of poorer outcome due to limited walking time. These patients may benefit from ongoing rehabilitation and outpatient physiotherapy services. This information will also provide a foundation for further research into interventions designed to optimise post-operative activity.

**Trial registration:**

ACTRN12616000747426, retrospectively registered 7th June 2016.

## Background

Low back pain is the leading cause of disability worldwide, with both the rate of low back pain and the associated burden of disability expected to increase as the global population ages [1]. Clinical guidelines consistently recommend conservative management of low back pain, however surgical intervention may be indicated where conservative management is not successful [2]. While there is a growing body of evidence to support surgical management of low back conditions [3–5], up to 40 % of patients continue to report no or minimal improvement in post-operative function [6]. This figure highlights the need for evidence based, effective rehabilitation programs designed to optimise post-operative recovery.

Physiotherapy is a common component of the management of patients undergoing lumbar spinal surgery at the majority of hospitals in Australia and the UK [7–9]. The goals of physiotherapy intervention during the inpatient admission consistently focus on achieving independence with mobility and functional tasks, and providing advice and education about post-operative walking and physical activity [7–9]. The specific interventions required to achieve these goals however, are poorly understood. There is very little research to guide physiotherapy intervention in the acute post-operative period [10, 11], with considerable variability in the advice provided to patients regarding post-operative walking and general activity [7–9, 12].

There are a growing number of studies aimed at identifying factors that predict outcome following lumbar spinal surgery. These include patient demographics (age [13], smoking status [14–16]), co-morbidities (diabetes [14, 16, 17], obesity [14, 18]), impairments (pain and sensory changes [14]), and psycho-social factors (depression [19, 20], fear avoidance [21]). These factors play an important role in selecting patients appropriate for surgical intervention. There is however, limited scope to modify any of these variables particularly in the acute post-operative phase, to influence patient rehabilitation or functional recovery.

Clinical guidelines for the management of low back pain consistently recommend staying active [2] with evidence suggesting that maintaining an active lifestyle leads to reduced pain and improved functional outcome [22]. It is not known whether this positive association can be translated into the post-surgical population, or more specifically, whether people who participate in more physical activity have better outcomes following surgery. In other post-surgical populations, evidence suggests that early and increased walking improves functional outcome and reduces the rate of post-operative complications [23]. It is therefore likely that increased walking immediately following lumbar spinal surgery leads to similarly improved outcomes.

Accelerometers are becoming an increasing popular method of quantifying physical activity, and have been shown to provide an accurate measure of step count, time spent walking and distance walked. [24–26] Two recent studies have used accelerometry to describe the improvement in physical activity following lumbar spinal surgery. Mobbs et al. [27] reported a significant improvement in step count and distance walked three months after lumbar spinal surgery, and Schulte et al. [28] reported a significant improvement in step count three months after surgery for lumbar stenosis. There are however, no known studies describing walking immediately following spinal surgery, or how the amount of walking in this period impacts longer-term functional recovery.

We know that gait assessment, and advice regarding walking and return to physical activity already forms a key component of physiotherapy intervention immediately following lumbar surgery. Establishing how much walking patients currently do, and how walking in the period immediately following surgery impacts longer term functional outcome will enable physiotherapists to individualise patient management to achieve optimal outcomes. It will also help to identify patients who are unable to achieve the minimum amount of walking associated with improved outcomes, and who may therefore require more intensive rehabilitation programmes.

## Method

### Aims

This research will investigate the relationship between the time spent walking in the week following lumbar surgery, and recovery of physical function. The primary aim is to establish whether the amount of walking patients do in the week following lumbar spinal surgery predicts improvement in function at six months. The data collected will also be used to generate an activity profile to describe the overall patterns of activity in the first post-operative week, and to identify factors that may influence the amount of activity patients undertake.

The research questions are:Does the amount of time spent walking during the week after lumbar spinal surgery predict improvement in function at six months?What proportion of time do patients spend performing active tasks (standing and walking) compared to sedentary behaviour (sitting and lying) in the week following lumbar spinal surgery?Is the amount of time spent walking in the first post-operative week influenced by restricted pre or post operative physical function, post-operative pain or complications, or the need for supervision while walking?

### Design

This study will be a prospective cohort study design. Ethics approval from the St Vincent’s Hospital Melbourne Human Research Ethics Committee’s has been obtained (Reference: LRR 098/15).

### Participants

Participants will be recruited from St Vincent’s Private Hospital, Fitzroy (SVPHF) over a six-month period. All patients aged 18 years and older undergoing surgery for the management of a disc prolapse, degenerative disc disease, lumbar spinal stenosis and/or degenerative spondylolysthesis will be invited to participate. There will be no restriction on the nature or duration of pre-operative symptoms. Patients will be excluded if they are undergoing surgery for the management of lumbar fractures or tumours, have a history of dementia or cognitive impairment or an inability to provide informed consent, or have a history of a neurological or musculoskeletal condition resulting in progressive impairment of physical function (for example, multiple sclerosis or rheumatoid arthritis). In cases where surgery includes both lumbar and thoracic vertebrae, patients will be eligible if 50 % or more of the vertebra involved are in the lumbar region.

### Study procedure

#### Recruitment and sample size

The recommended sample size for logistic regression analysis is a minimum of 5 outcome events per predictor variable (EPV) [29]. The maximum number of variables to be analysed in this study is 15 giving a minimum sample size of 150. Based on expected admissions to the treating institution over the recruitment period, it is expected that this will provide an estimated recruitment pool of 300 eligible participants and sample size of approximately 250 participants. This proposed sample size allows for variation in EVP, missing data and participants lost to follow-up.

Patients undergoing lumbar spinal surgery will be identified from the surgical lists. All eligible patients will be provided with an information pack containing a participant information statement, consent form, withdrawal of consent form and baseline outcome measures. The research physiotherapist will contact potential participants during the week prior to surgery to confirm eligibility and respond to any questions. Written consent will be obtained from all participants. Consent forms and baseline outcome measures will be collected from participants following admission to hospital. Demographic data and information about the surgical procedure will be collected from the participant and patient records during admission.

Following surgery, all participants will be fitted with an activPAL3 accelerometer (PAL technologies) to be worn for the first seven post-operative days, commencing the morning after the day of surgery. As per the manufacturer instructions, the accelerometer will be fixed to the upper thigh using a waterproof transparent Tegaderm dressing. This can then remain in place for the seven-day monitoring period, with a daily review to check for discomfort or irritation. This method of fixing the accelerometer to the thigh eliminates the need for participants to remove and apply the monitoring device for showering and sleeping, it does not require participants to wear a waist band or belt that would sit across the site of the lumbar surgery.

Where participants are discharged during the seven-day monitoring period they will be provided with information regarding the use and removal of the accelerometer, and a reply paid envelope to return the accelerometer to the researcher.

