#### Relationship between time spent walking and outcome

Multivariable logistic regression analysis will be used to investigate the relationship between the time spent walking in the first week after surgery and outcome at six months using SPSS software. The dependent variable in the logistic regression model will be the change in score on the ODQ, SF-36 (PCS), NRPS (back) and NRPS (leg) between baseline and six months. The change in scores on the ODQ, SF-36 (PCS) and NRPS will be dichotomised based on the threshold required to demonstrate a substantial clinical benefit.

Thresholds required to meet the minimum clinically important difference (MCID) have been identified for the ODQ, the SF-36 (PCS) and the NPRS [41] (Table 2). In addition, thresholds required to obtain a substantial clinical benefit (SCB), where patients report a major improvement in symptoms, have been defined for the ODQ, SF-36 (PCS) and NRPS in the lumbar fusion population [42] (Table 2). For the purpose of this study it has been assumed that SCB following lumbar fusion surgery provides a fair estimate of substantial clinical benefit following lumbar surgery in general. These thresholds allow the change in scores to be categorised as minimal improvement (below MCID threshold), moderate improvement (above MCID threshold, below SCB threshold) and substantial improvement (SCB threshold or greater).

**Table 2 Tab2:** MCID and SCB thresholds

Outcome measurement tool	MCID (points change)	SCB (points change)
ODQ	10	18.8
SF-36 (PCS)	4.9	6.2
NPRS (back)	2	2.5
NRPS (leg)	2	2.5

As all participants in this study are undergoing surgery with the aim of improving pain and physical function, it expected that the majority of participants in this study will report an improvement in scores above the MCID threshold. Therefore the SCB threshold will be used to analyse the impact of walking time on outcome (minimal/moderate improvement compared to substantial improvement). For each of the four dependent variables a multivariable logistic regression model will be generated comparing participant outcome relative to the SCB threshold.

With the exception of pre-operative function and surgical procedure, all confounding variables will be dichotomised (Table 3).

**Table 3 Tab3:** List of independent variables and classification for statistical analysis

	Classification				
1. Post-operative activity	Time spent walking (minutes)				
2. Age	1. < 65 years	2. ≥ 65 years			
3. Gender	1. Male	2. Female			

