4. Current smoking status	1. Non-smoker	2. Smoker			
5. Obesity	1. BMI < 30	2. BMI ≥ 30			
6. Diabetes	1. Not diabetic	2. Diabetic			
7. Depression	1. PHQ-9 < 10	2. PHQ-9 ≥ 10			
8. Anxiety	1. GAD-7 < 10	2. GAD-7 ≥ 10			
9. Duration of pain/symptoms	1. < median (months)	2. ≥ median (months)			
10. Neurological deficit	1. No deficit	2. Neurological deficit			
11. Pre-operative activity	1. IPAQ-SF - Mod/high	2. IPAQ-SF - low			
12. Pre-operative mobility	1. ODQ (section 4) < 3	2. ODQ (section 4) ≥ 3			
13. Surgical procedure	1. Decompression	2. Disc surgery	3. Fusion		
14. Multi-level surgery	1. Single level surgery	2. Multi-level surgery			
15. Preoperative function (ODQ%)	1. 0–20	2. 21–40	3. 41–60	4. 61–80	5. 81–100

Bivariate analyses will be carried out to assess the association between each confounding variable and each outcome measure. The variables that have an independent association with outcome will be included in the final regression model. Analysis of correlation between the independent variables will be carried out to assess for multicollinearity. Where variables are highly correlated, either the more relevant variable or the variable with the more complete data set will be retained in the final regression model [43].

Missing independent variable data will be managed based on the quantity of missing data per participant and per variable. In the case of missing or incomplete accelerometry data, participants will be removed from analysis where three or more days of recordings are missing. In the case of one to two days of missing data, the time spent walking each day will be estimated based on the mean daily walking time of the total sample population. Comparisons will be made between the characteristics of participants with and without missing data to ensure minimisation of bias [43]. The underlying assumptions of the model will be assessed using the SPSS software “goodness of fit” testing.

Bivariate analysis will be used to examine the association between post-operative walking time, and both patient satisfaction and post-operative complications as reported at six months.

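### The stated minimum of 150 is a best case: Table 3 defines up to 19 parameters, so the allowance within 250 is much narrower than it looks

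*Protocol article*

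**What the plan says.** The sample-size paragraph of the protocol article (Recruitment and sample size) starts from this rule: "The recommended sample size for logistic regression analysis is a minimum of 5 outcome events per predictor variable (EPV". It then gives the only calculation in the document: "The maximum number of variables to be analysed in this study is 15 giving a minimum sample size of 150". From expected admissions it derives an "estimated recruitment pool of 300 eligible participants and sample size of approximately 250 participants", and it describes the surplus over 150 as a safety margin: "This proposed sample size allows for variation in EVP, missing data and participants lost to follow-up". It gives no event proportion and no loss rate.

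The analysis section (Relationship between time spent walking and outcome) defines the event: "Therefore the SCB threshold will be used to analyse the impact of walking time on outcome (minimal/moderate improvement compared to substantial improvement". A separate logistic model is planned for each of four outcomes: ODQ, SF-36 PCS, back pain and leg pain. On coding it says: "With the exception of pre-operative function and surgical procedure, all confounding variables will be dichotomised". In Table 3, the row "13. Surgical procedure" has three classes and the row beginning "15. Preoperative function (ODQ" has five bands.

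**The concern.** The rule is about events, while the conclusion is about participants. Moving from one to the other needs the proportion in the less frequent outcome class, and the paragraph does not give it. The count of 15 also treats every row of Table 3 as one model term, although the plan keeps two rows as multi-category variables.

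Both simplifications lower the stated minimum. The reader is told that 250 covers variation in events per variable, missing data and loss to follow-up. If the true minimum is well above 150, that cover is thinner than it appears, and four models could be reported as adequately sized when they are overfitted by the plan's own rule.

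**Working it through.** **Inputs.** Five events per variable, 15 variables, minimum 150 and planned 250 come from Recruitment and sample size. The coding of each variable comes from Table 3. Event proportions and loss rates are not in the document, so ranges are used and are assumptions.

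**Step 1: reproduce 150.** With k parameters and a proportion f in the smaller outcome class, n = 5 × k / f. For k = 15, 5 × 15 = 75 events, and 75 / 0.50 = 150. The figure reproduces exactly, but only at f = 0.50. The smaller class cannot exceed half, so 0.50 is the most favourable value possible. (Ten participants per variable is the same arithmetic.)

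**Step 2: count parameters from Table 3.**
- Walking time, continuous: 1
- Twelve two-class confounders (rows 2 to 12 and row 14): 12
- Surgical procedure, three classes: 2
- Pre-operative ODQ, five bands: 4

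Total 1 + 12 + 2 + 4 = 19, so 5 × 19 = 95 events. At n = 150 and f = 0.50 there are 75 / 19 = 3.95 events per parameter. With baseline ODQ as one continuous term, the total is 1 + 12 + 2 + 1 = 16, and 5 × 16 = 80 events.

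**Step 3: analysable participants needed (5k / f, rounded up).**

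| Smaller class | 15 terms (75 events) | 16 terms (80 events) | 19 terms (95 events) |
|---|---|---|---|
| 50% | 150 | 160 | 190 |
| 40% | 188 | 200 | 238 |
| 35% | 215 | 229 | 272 |
| 30% | 250 | 267 | 317 |

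**Step 4: smallest f at which 250 enrolled still gives 5 events per parameter, 5k / n.**

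| Loss (assumed) | n analysed | 15 terms | 16 terms | 19 terms |
|---|---|---|---|---|
| 0% | 250 | 30.0% | 32.0% | 38.0% |
| 10% | 225 | 33.3% | 35.6% | 42.2% |
| 20% | 200 | 37.5% | 40.0% | 47.5% |
| 30% | 175 | 42.9% | 45.7% | 54.3% (impossible) |

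**Step 5: tolerable loss from 250.** At f = 0.50, the protocol's count allows 1 − 150/250 = 40%, and 19 parameters allow 1 − 190/250 = 24%. At f = 0.40, the figures are 1 − 187.5/250 = 25% and 1 − 237.5/250 = 5%.

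Some loss is to be expected under the plan's own procedures. The six-month questionnaires come back by mail, discharged participants post the device back, and anyone with three or more days of missing recordings is removed from analysis.

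**The case against.** The strongest reply has four parts.

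- **The figure reproduces, and an article may leave the event rate to a fuller document.** It is true that 150 is not a slip of multiplication. But the article does print the calculation and calls the result a minimum, and that result conflicts with the coding in its own Table 3. This is more than omitted detail.
- **Fifteen is a maximum, and screening will shrink the model.** The fitted model may well be smaller, and a reader should not infer that 19 terms will certainly be fitted. But screening candidates against the outcome still uses up information, so the candidate count is the right planning basis, and the protocol itself sized on the maximum. Removal for collinearity is different because it does not use the outcome. Pre-operative mobility is taken from an ODQ item, so overlap with baseline ODQ is likely. Dropping mobility leaves 19 − 1 = 18 parameters, 90 events and 90 / 0.50 = 180 participants, still above 150. Dropping the ODQ bands instead would leave 19 − 4 = 15. The plan commits to neither.
- **The ODQ bands might enter as one ordinal score.** That would give 16 parameters and a minimum of 160 at 50%, close to 150. Table 3 lists five classes and states no trend coding, so 19 is the count as classified, and it is properly a ceiling.
- **The extra 100 participants already cover this.** In part they do. One might infer that 250 is too few or that 5 events per parameter will be missed. The document does not support that, because it gives neither an event rate nor a loss rate. Its background figure of up to 40% concerns no or minimal improvement, not failure to reach substantial clinical benefit, so it cannot fill the gap.

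**Conclusion.** The point holds as a correction to the stated minimum and to the margin claimed from it. The figure of 150 rests on two unstated best-case conditions. With Table 3 as classified, the minimum is 190 even at an even split, and 238, 272 and 317 analysable participants at 40%, 35% and 30% in the smaller class. Enrolling 250 meets 5 events per parameter at 50% with up to 24% loss and at 40% with up to 5% loss. Below 38% it falls short even with no loss.

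So 5 events per parameter is not secured at 250, which is different from saying that it will not be met. The result assumes indicator coding of the two multi-category variables and counts all candidates. The loss and event rates are illustrative ranges. The events-per-variable threshold is the protocol's own rule of thumb, so small shortfalls against it carry little weight. The study's feasibility is not in question.

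**What to change.** 1. Restate the minimum as 5 × candidate parameters / proportion in the smaller class. Do this for each of the four outcomes, with the assumed event and loss rates shown, and let the least favourable outcome govern.
2. Enter baseline ODQ, which is already collected, as a single continuous term. This gives 16 parameters and 80 events: 160 analysable participants at 50%, 200 at 40%, 229 at 35% and 267 at 30%.
3. Replace the general claim about allowance with the point at which 250 no longer gives 5 events per parameter: 32% in the smaller class with no loss, or 40% with 20% loss. The recoding does not secure the rule below those values, and the text should say so.

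The cost is revised text and one coding decision, with no additional patients. The stated minimum becomes less favourable. A single continuous term also assumes that the log-odds are linear in baseline ODQ. That should be checked, and any extra term counted. A detectable odds ratio for walking time could be added, but it would need inputs that the document does not give and is not part of this correction.

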#### Six-month follow-up

At 6 months following surgery participants will be sent follow-up outcome measures, to be returned to the researchers by mail.

All participants will receive routine inpatient physiotherapy management. As part of routine management participants are encouraged to walk at least 3 times daily over a comfortable distance, increasing both the frequency and distance as able. An exercise program is also commenced within the first 3 days following surgery, and includes activation of deep core muscles in a supine position, exercises to gently increase range of motion including lumbar rotation and neural slides, and lower limb strengthening. A single researcher will conduct all participant communication, measurement, data collection and application of accelerometers.

